### Efficacy Assessments/Measurement of Effect

Therapeutic improvement, in our study, was defined as expected by statistically significant changes in some of our primary as well as secondary outcomes. To capture the progress in clinical improvement, we chose 2 validated scales that show high reliability and sensitivity to schizophrenia symptomatology—the PANSS and the NSA. The CFS was added as an additional measure for the executive function. We considered participants to be good responders to the intervention if there was an increase in PANSS General Scores higher than or equal to 20% of their baseline scores at the end of the intervention, with an improvement in scores of the PANSS Positive and PANSS Negative scales of at least 15% compared with the baseline. The therapeutic improvement also included a 20% decrease in scores for the NSA scale and a 20% increase in CFS scores at the end of the intervention, compared to baseline.

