### Statistical Outcomes

#### Primary Outcome Measures

EEG gamma oscillations are fast neural rhythms linked to higher-order cognitive functions (attention, working memory, executive control, and consciousness). In the prefrontal cortex, gamma EEG activity is associated with working memory maintenance, cognitive flexibility, top-down attention control, and integrating information across cortical areas. Altered prefrontal gamma observed in schizophrenia. EEG measurement of gamma activity in the prefrontal cortex refers to detecting brain oscillations in the gamma frequency band (typically 30-100 Hz, often subdivided into low gamma: 30-50 Hz, and high gamma: 60-100 Hz) from scalp electrodes positioned over prefrontal areas. In a within-subject design, we will compare gamma power across time windows (pre- and postintervention). In a between-subject design, we use mixed models or *t* tests on summary metrics (mean power in time×freq window).

PANSS is a standardized clinical interview that rates the presence and severity of positive and negative symptoms and general psychopathology for people with schizophrenia within the past week [32]. The scale consists of 30 items: 7 positive, 7 negative, and 16 general psychopathology symptoms. The symptom severity for each item is rated according to a 7-point scale (1=absent to 7=extreme) to best describe the symptom’s presentation. The clinical interview takes approximately 45 minutes. The patient is rated from 1 to 7 on 30 different symptoms based on the discussion and reports of family members or primary care hospital workers. As 1 is the lowest score for each item, a patient cannot score lower than 30 for the total PANSS score. Scores are often given separately for positive items, negative items, and general psychopathology. [Time frame: PANSS will be applied at visit 1, screening (week 0); visit 4, end of intervention (week 17); visit 5, follow-up 1 (week 21); and visit 6, follow-up 2 (week 29).]

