The NSA-16 assesses the presence, severity, and range of negative symptoms associated with schizophrenia [33]. For rapid clinical assessment or screening of patients for negative symptoms, the NSA-4 was developed as a simplified version, retaining only 4 of the 16 items: restricted speech quantity, reduced emotion, reduced social drive, and reduced interests. Each of the 4 items and the overall global negative symptoms is rated on a 1- to 6-point scale, where “1” represents no reduction from normal behaviors associated with the item and “6” represents a severe reduction in or absence of the behavior, with markedly impaired functionality. With respect to overall accuracy and predictive validity, the NSA-4 is comparable to the NSA-16. [Time frame: NSA-16 will be applied at visit 2, baseline (week 1); visit 4, end of intervention (week 17); visit 5, follow-up 1 (week 21); and visit 6, follow-up 2 (week 29).]

The CFS assesses cognitive flexibility as a factor that facilitates the individual’s adaptability toward events [34]. Cognitive flexibility refers to a person’s awareness of the existence of different communication styles in every situation, as well as their willingness and self-efficacy to employ these styles. The scale has 12 items pertaining to the 3 elements of cognitive flexibility: a person’s awareness of alternative communicative styles, willingness to be communicatively flexible, and self-efficacy in being communicatively flexible. The scale uses a 6-point Likert-type scale for each item (with 6 as “strongly agree,” 5 as “agree,” 4 as “slightly agree,” 3 as “slightly disagree,” 2 as “disagree,” and 1 as “strongly disagree”). The total score was used to calculate a global score ranging from 12 to 72, with questions 2, 9, 11, and 12 being reverse-coded. A higher score indicates higher cognitive flexibility. [Time frame: CFS will be applied at visit 2, baseline (week 1); visit 3, midpoint of intervention (week 9); visit 4, end of intervention (week 17); visit 5, follow-up 1 (week 21); and visit 6, follow-up 2 (week 29).]

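### The good-responder rule asks for a rise in PANSS General, which on the protocol's own scoring is worsening; the criterion should be a decrease

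*Protocol article*

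**What the plan says.** The Efficacy Assessments/Measurement of Effect section of the protocol article gives the document's only participant-level definition of response. A good responder must show an "increase in PANSS General Scores higher than or equal to 20% of their baseline scores at the end of the intervention". The second condition concerns the other two PANSS subscales, where the rule asks for "improvement in scores of the PANSS Positive and PANSS Negative scales of at least 15% compared with the baseline". A separate sentence then adds, as part of therapeutic improvement, a "20% decrease in scores for the NSA scale and a 20% increase in CFS scores at the end of the intervention".

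The Primary Outcome Measures section describes the scales. On PANSS: "The scale consists of 30 items: 7 positive, 7 negative, and 16 general psychopathology symptoms". Each item is "rated according to a 7-point scale (1=absent to 7=extreme"), and "a patient cannot score lower than 30 for the total PANSS score". The Cognitive Flexibility Scale (CFS) has a "global score ranging from 12 to 72", with higher scores meaning greater flexibility. The Objectives section expects CBTp to improve PANSS, NSA-16 and CFS scores.

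**The concern.** On PANSS, more points mean more severe symptoms. A responder rule built on a rise in PANSS General therefore selects people whose general psychopathology has become worse. The same rule asks for improvement on the other two PANSS subscales, so its parts pull in opposite directions.

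What is at stake is the label given to individual participants. By 1 November 2025 the trial had enrolled 15 people (abstract, Results). Master's theses from preliminary data are expected by the end of 2026, and a preliminary or interim analysis is to support a funding application (Disseminations). Only participants are blinded (Enrollment and Randomization). If the direction is left uncorrected until someone tries to apply the rule, people who know the allocation will be repairing it with outcome data in view.

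**Working it through.** **Inputs, all from Primary Outcome Measures.** 7 Positive, 7 Negative and 16 General PANSS items, each scored 1 to 7. 12 CFS items, each scored 1 to 6. The cut-offs (20%, 15%, 20%) come from Efficacy Assessments/Measurement of Effect.

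**Step 1: reproduce the document's own ranges.** PANSS total minimum: (7 + 7 + 16) × 1 = 30, as stated. The subscale ranges follow: General 16 × 1 = 16 to 16 × 7 = 112; Positive and Negative each 7 × 1 = 7 to 7 × 7 = 49. CFS: 12 × 1 = 12 to 12 × 6 = 72, as stated. So PANSS gets worse as it rises, and CFS gets better as it rises.

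**Step 2: apply the rule as written.** The General criterion is: week-17 score ≥ 1.20 × baseline. A reduction criterion would be: week-17 score ≤ 0.80 × baseline.

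| General baseline | Rule as written | 20% decrease |
|---|---|---|
| 30 | 36 or more | 24 or less |
| 40 | 48 or more | 32 or less |
| 50 | 60 or more | 40 or less |

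The two conditions exclude each other at every baseline. Two made-up participants, both starting at General 40, Positive 20 and Negative 20, show the effect:

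- A ends at 30, 16 and 16. The falls are 25%, 20% and 20%. A fails, because General did not rise.
- B ends at 48, 17 and 17. General has worsened by 20% and the other two have fallen by 15%. B passes.

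**Step 3: how many would be labelled responders?** The document gives no baseline scores, so this can only be illustrated. A simulation of the three PANSS components assumed baseline mean (SD) 36 (8) for General and 18 (5) for Positive and Negative, a change SD of 0.7 times the baseline SD, mean improvement of 10% to 50% of the distance above the scale minimum, and correlations of 0.3 to 0.7. The rule as written labelled 0.02% to 0.4% as responders; with the direction corrected, 5% to 56%. Among 28 participants that is at most 28 × 0.004 = 0.1 expected responders, against 28 × 0.05 = 1.4 to 28 × 0.56 = 15.7.

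**Step 4: attainability once the direction is right (secondary).**

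- General: a 20% fall must not go below 16, so baseline must be at least 16 / 0.80 = 20. Baselines 16–19 cannot respond.
- Positive or Negative: 7 / 0.85 = 8.24. Baselines 7–8 cannot respond.
- CFS: 72 / 1.20 = 60. Baselines 61–72 cannot rise by 20%.

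**The case against.** The strongest reply is that this is one wrong word with an obvious intended meaning. The same sentence asks for improvement on Positive and Negative, the next asks for a decrease on the NSA, and the Objectives expect PANSS to improve. That is probably right about intent. It does not remove the error: the passage uses a rise, a fall and an improvement as distinct terms, its rise is correct for CFS, and nothing elsewhere overrides the General criterion.

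The reply on consequence stands. A reader might infer that the trial's responder result would be reversed. The document does not support that. No responder proportion appears among the primary or secondary outcomes, and the Sample Size section plans descriptive analyses with effect estimates and 95% CIs, using repeated-measures and mixed-design ANOVA and t tests. Literal use would give an almost empty and misclassified responder group, not a reversed comparison of arms.

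A reader might also infer from the scale limits that the percentages must be recalculated after subtracting each scale's minimum. That goes too far. Keeping 20% and 15% on such scores lowers the bar: at General 32 the required fall drops from 0.20 × 32 = 6.4 points to 0.20 × (32 − 16) = 3.2, and at Positive 10 from 0.15 × 10 = 1.5 to 0.15 × (10 − 7) = 0.45. That is a new definition of response. For the NSA-16 the document does not state a scale minimum at all; its 1-to-6 rating is described for the four-item version and the global rating.

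Nor does the entry requirement of one residual positive symptom make response generally impossible. One Positive item rated 3 with the other six at 1 gives 9, and a fall to 7 is 2/9 = 22%, which meets the 15% cut-off. It is also unclear whether the NSA and CFS cut-offs belong to the good-responder rule, since they sit in a separate sentence.

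**Conclusion.** The PANSS General criterion is wrong as written. It counts a worsening of at least 20% towards response and excludes anyone who improves by any amount on that subscale. This follows from the article's own scoring and needs no assumption. It should be corrected before use, because it is the only participant-level response rule in the document.

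The reach is limited. Analyses of continuous PANSS, NSA-16 and CFS scores are not touched, and no listed outcome depends on the rule. The simulated responder percentages rest entirely on assumed baselines and changes and serve only to show that literal use yields almost nobody.

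The unreachable ranges (General 16–19, Positive or Negative 7–8, CFS 61–72) are arithmetically firm. How many participants fall in them is unknown, so they call for a reporting note and not for new thresholds.

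**What to change.** Required: in Efficacy Assessments/Measurement of Effect, change the PANSS General criterion to a decrease of at least 20% from baseline at the end of the intervention. State in the same sentence that improvement on PANSS Positive and Negative means a decrease of at least 15% from baseline. Date the correction and make it before any responder classification, including any made for theses or a preliminary analysis.

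Cost: a wording amendment. No new data or visits, and no change to sample size or to the continuous-score analyses.

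Secondary: if a responder summary is reported, give by arm the number of participants whose baselines make a cut-off unreachable (General 16–19, Positive or Negative 7–8, CFS 61–72). Subtracting the scale minimum is an option for the sponsor, but it lowers the change required and would mean reconsidering the cut-offs, so it is not part of this correction.

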### Safety Considerations

An adverse event (AE) is any untoward medical occurrence in a patient administered an intervention (tACS in our specific project). An AE does not necessarily have a causal relationship with the treatment. An AE can be any unfavorable and unintended sign (including an abnormal finding or lack of expected interventional action), symptom, or disease temporally associated with the use of a tACS, whether or not related to tACS (definition based on the International Council for Harmonisation [ICH]). This includes any occurrence that is new in onset or aggravated in severity from the baseline condition, or abnormal results of any diagnostic procedures that are conducted within clinical practice.

An adverse intervention reaction (AIR) is defined as a response to an intervention (eg, tACS application) that is noxious and unintended. The phrase “response to an intervention” means that a causal relationship between the intervention and an AE is at least a reasonable possibility. The phrase “a reasonable possibility” means that there are facts, evidence, or arguments to support a causal association with the intervention. An AIR, in contrast to an AE, is characterized by the fact that a causal relationship between the intervention and the occurrence is suspected. All AEs judged by either the reporting physician or the sponsor as having a reasonable causal relationship to an intervention qualify as AIRs.

The AEs expected from tACS are a very mild tingling sensation, fatigue, a light itching skin sensation under the stimulus, a mild headache, and dizziness, all of which disappear just after stimulation. With tACS, no persistent AEs have been reported; however, the AEs associated with repetitive tACS application remain unclear. In this type of stimulation technique, no serious adverse effects were reported. Some questionnaires may ask about stressful events in their life, which may cause them to feel discomfort or recall past experiences that upset them. If they find the questionnaire content distressing, they are encouraged to inform the study coordinator immediately or at a later time.

A serious adverse event (SAE), based on ICH and EU Guidelines on Pharmacovigilance for Medicinal Products for Human Use, is any untoward medical occurrence that at any dose (with extending the meaning to the tACS intervention):

All SAEs assessed by the participating physician should be recorded in the participant’s source documents. For reports of hospitalization, it is the sign, symptom, or diagnosis which led to hospitalization that is the serious event for which details must be provided. Any event requiring hospitalization (or prolongation of hospitalization) that occurs during the study must be reported as an SAE, except hospitalizations for the following: (1) hospitalizations not intended to treat an acute illness or AE (eg, social reasons such as pending placement in a long-term care facility); (2) surgery or procedures planned before entry into the study (should be documented in the case report form [CRF]) [note: hospitalizations that were planned before the start of data collection, and where the underlying condition for which the hospitalization was planned has not worsened, will not be considered as SAEs]; (3) any AE that results in a prolongation of the originally planned hospitalization is to be reported as a new SAE; and (4) the cause of death of a participant in a study, whether the event is expected or associated with the intervention, is considered as an SAE.

### Pregnancy

Pregnancy here is no contraindication of tACS or CBTp during pregnancy. However, a participant in this special circumstance could have a different response to the intervention, influencing our final results. If a participant becomes pregnant during the study, data specified in the “data collection schedule” that is collected as part of the participant’s standard of care will continue to be recorded in the CRF for the applicable time points, but the participant will be withdrawn from the study.

### Statistical Considerations: Sample Size

This is a pilot randomized study with 28 participants (14 per arm). The primary goals are to evaluate recruitment feasibility, acceptability, and safety, and to produce unbiased estimates of the standard deviation and preliminary effect sizes of the primary outcome to inform sample-size calculation for a future definitive trial [31]. A target of 28 participants is consistent with common pilot rules-of-thumb (approximately 12-20 per arm) and provides sufficient precision to estimate recruitment and retention rates and the outcome variance. This pilot is not powered for hypothesis testing of efficacy (with n=14 per group, the minimal detectable standardized effect is large, ~*d*=1.1); outcome analyses will therefore be descriptive and will report effect estimates with 95% CIs as inputs for future sample-size calculations. To allow for expected attrition (approximately 15%-20%), we will recruit up to 33-40 participants. The generalizability of our findings is limited by the small sample size (n=28) and recruitment from a single treatment site. Patients in this cohort may differ from the broader schizophrenia population with respect to illness chronicity, symptom severity, comorbid psychiatric or medical conditions, and sociodemographic characteristics. In addition, the specialized treatment context may not reflect the experiences of individuals receiving care in community or primary care settings, where clinical resources and treatment approaches may vary. These factors restrict the extent to which the present results can be applied to other patient populations. Replication in larger, multisite, and more heterogeneous cohorts will be essential to establish the robustness and external validity of the findings.

The statistical analysis plan will use SPSS (version 29, IBM Corp) for the main tests, including effect size (Cohen *d*) and a 95% CI: repeated measures, mixed design analysis of variance, and *t* tests for two-group comparisons. Sex and gender differences will be examined using regression models that include biological sex, BSRI masculinity and femininity scores, and their interaction terms, with exploratory subgroup analyses based on BSRI classifications.

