**Methods:**

This is a pilot, prospective, randomized, repeated-measures, single-blind study design. We expect to enroll 28 participants randomly assigned to one of two treatment arms: arm 1 (tACS/CBTp, n=14) or arm 2 (sham tACS/CBTp, n=14; tACS is sham, but CBTp is active). The intervention with active or sham tACS/CBTp will take place weekly for 16 weeks. Primary outcome measures—electroencephalogram, Positive and Negative Syndrome Scale, 16-item Negative Symptom Assessment, and Cognitive Flexibility Scale—will evaluate the efficacy of treatment at the end of the intervention and at the two follow-ups. We will use SPSS (version 29, IBM Corp); the main tests will include repeated measures and mixed design ANOVA.

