### Objectives

This study compares the effects of a harmless, low-voltage electrical stimulation (tACS) with placebo stimulation (sham tACS) applied for 20 minutes at the beginning of the CBTp session to increase the efficacy of psychotherapy in people living with schizophrenia.

Primary objectives are to determine whether (1) the new intervention protocol using tACS will enhance the EEG activity, expecting that CBTp will enhance EEG activity in clients with schizophrenia at the end of therapy for both groups, with a better outcome for the group with active tACS stimulation; and (2) tACS applied at the beginning of the CBTp sessions in people with schizophrenia will predict better responses to therapy (compared with the sham tACS/CBTp). CBTp is expected to improve the scores of the PANSS, NSA-16, and Cognitive Flexibility Scale (CFS).

The secondary objectives are to determine whether (1) there will be an improvement of level of functioning and quality of life in both intervention groups, with a superior outcome for the group receiving tACS intervention (psychological and psychosocial tests); (2) higher in-session HRV predicts a better response to CBTp (the expectation is that baseline HRV will predict symptom improvement and increase over the course of therapy); and (3) the response to tACS/CBTp intervention is gender specific; considering that cognitive and emotional status is gender dependent, we expect that the therapeutic response could be gender specific.

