## Methods

### Trial Design

#### Description

This is a prospective, randomized, repeated-measures, single-blind study design. Preintervention, eligible participants will be randomly assigned to one of two treatment arms: arm 1 (tACS/CBTp, n=14) or arm 2 (sham tACS/CBTp, n=14; tACS is sham, but CBTp is active). In the intervention (16 weeks), participants in arms 1 and 2 will receive once-weekly tACS/CBTp or sham tACS/CBTp. Individuals with schizophrenia (*DSM-5* [*Diagnostic and Statistical Manual for Mental Disorders* {Fifth Edition} criteria) stratified by age and sex. The investigators expect 150 potentially eligible patients from Providence Care Mental Health Services, with 33-40 participants consenting to participate and 28 participants undergoing the research activities (see Figure 1).

Participants will be randomized 1:1 to one of two arms and stratified by age (18-30, 31-55, and >60 years) and by sex (male or female).

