### Disseminations

Aside from the current published protocol and the first scoping review on this topic [18], the investigators anticipate publishing up to 5 new peer-reviewed publications and presenting the results at different scientific events. Two graduate students are team members of this research, and by the end of 2026, they will write their master's theses from the preliminary data of this clinical trial. This pilot study aims to test and redefine our research methods, procedures, and feasibility of the main study. Based on the preliminary/interim analysis, we intend to apply for funding to further expand on the correlation between specific frequency brain stimulation and clinical outcomes in schizophrenia. Adding brain imaging evidence will help us to prove the efficacy of our new intervention protocol.

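### The primary purpose is stated in two ways that do not fit together, and the feasibility and acceptability goals called primary are not declared as outcomes

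*Protocol article*

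**What the plan says.** **Pilot purpose.** Under Statistical Considerations: Sample Size, "The primary goals are to evaluate recruitment feasibility, acceptability, and safety". The same sentence adds a further goal: estimating the SD and preliminary effect sizes of the primary outcome for a later trial. The section says the study is not powered to test efficacy and that "outcome analyses will therefore be descriptive". It also names recruitment and retention rates as quantities to be estimated. Disseminations repeats the pilot aim: "This pilot study aims to test and redefine our research methods, procedures, and feasibility of the main study".

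**Efficacy purpose.** The Objectives section reads "Primary objectives are to determine whether (1) the new intervention protocol using tACS will enhance the EEG activity", followed by whether active tACS gives a better response than sham. The abstract says the primary measures (EEG, PANSS, NSA-16, CFS) "will evaluate the efficacy of treatment at the end of the intervention and at the two follow-ups". Efficacy Assessments/Measurement of Effect adds: "Therapeutic improvement, in our study, was defined as expected by statistically significant changes in some of our primary as well as secondary outcomes".

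**Outcome lists.** The primary, secondary and other prespecified outcomes cover EEG, clinical and cognitive scales, heart rate variability, functioning, quality of life, alliance and screening tools. None is recruitment, retention, session completion, tolerability or acceptability.

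**The concern.** The two statements lead to different reports. Under the pilot purpose, the main results are how many consented, stayed and completed the sessions, what harms occurred, and how variable the outcomes were. Under the efficacy purpose, the main results are active-versus-sham contrasts on four measures, and the efficacy section invites the team to call a significant one therapeutic improvement. The abstract and objectives, which readers meet first, give only the second purpose.

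At stake is the trial's main conclusion. A trial that disclaims power for efficacy could still report significance tests as its primary result, while the goals used to justify a pilot of 28 would have no declared outcome against which to report.

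**Working it through.** **1. The sections side by side**

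- Primary purpose: feasibility, acceptability, safety, SD and effect size (sample size section) against efficacy versus sham (abstract, Objectives).
- Analysis: descriptive, with effect estimates and 95% CIs (sample size section) against improvement judged by significance (efficacy section). The sample size section itself goes on to list mixed-design analysis of variance and t tests among its main tests.
- Overlap: EEG, PANSS, NSA-16 and CFS do serve the SD and effect-size goal. The conflict is over what those measures are for, and over the remaining goals.

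**2. Stated goals against declared outcomes**

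- SD and effect size: served by the four primary measures.
- Safety: events are recorded under Safety Considerations, outside the outcome lists.
- Recruitment and retention: named in the sample size section, reviewed by the monitor from screening and enrolment logs and withdrawals (Monitoring Plan), and documented on withdrawal forms (Criteria for Withdrawal). Not listed as outcomes.
- Acceptability: no measure in the outcome lists or the study calendar. The WAI-SR measures therapeutic alliance. The PETiT measures attitude to medication and psychosocial functioning.

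**3. The stated detectable effect**

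Inputs: 14 per arm and d of about 1.1 (sample size section). Level and power are not stated; I assume two-sided 0.05 and 80%.

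- Two-sample t test: df = 2 × 14 − 2 = 26; critical t = 2.056; noncentrality = d × √(14/2) = 1.1 × 2.646 = 2.91.
- Power at d = 1.1 is 80.0%, and solving for 80% power gives d = 1.100. The figure is correct under these assumptions.

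**4. What 14 per arm can show on the efficacy measures**

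- 95% CI half-width for a difference in means, in SD units: 2.056 × √(2/14) = 2.056 × 0.378 = 0.78.
- By the same arithmetic, an unadjusted t test reaches p < 0.05 only if the observed difference is at least about 0.78 SD. A significant result would therefore come with a large apparent effect, whatever the true one.
- Pooled SD with 26 df: 95% limits are s × √(26/41.92) = 0.79s to s × √(26/13.84) = 1.37s. This is useful for planning, though imprecise.

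**5. What the logs could give**

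Exact (Clopper-Pearson) 95% CIs on the article's planning counts:

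- Consent among the 150 expected potentially eligible: 33/150 = 22% (16% to 29%); 40/150 = 27% (20% to 34%).
- Retention if 28 remain: 28/33 = 85% (68% to 95%); 28/35 = 80% (63% to 92%).
- Retention if 28 is the number randomised and, for illustration, 23 remain (18% lost, inside the stated 15% to 20%): 23/28 = 82% (63% to 94%).

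These rates can be estimated from records already kept, although imprecisely. Nothing can be computed for acceptability.

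**The case against.** The strongest reply is that the two statements partly overlap. SD and effect-size estimation is itself a primary goal, and the listed primary measures serve it directly. Recruitment and retention are named and logged, the stimulator records each session (Trial Intervention, tACS), and safety events are collected. That stands. What is missing is mainly a declaration, plus any measure of acceptability.

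A reader might go further and infer four things that the documents do not support:

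- *That the pilot cannot inform whether a larger trial should proceed.* It can in part, because the records and the variance estimates will exist.
- *That the absence of progression criteria is a defect.* They may sit in the full protocol or analysis plan, which is not shown.
- *That recruitment is miscounted because two screening failures are among the 15 enrolled.* The article gives the full split: 12 in intervention, 2 screening failures, 1 withdrawal. Nor is 12 of 13 a retention rate, because it is a snapshot of people still in treatment.
- *That the registered primary outcomes should be demoted.* Only participants are blinded and recruitment is under way, so replacing those outcomes now would raise its own concern about outcome switching.

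None of this removes the conflict between the sample size section and the abstract, objectives and efficacy definition.

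**Conclusion.** The point holds as an inconsistency of purpose with a practical consequence. The sample size section describes a descriptive pilot; the abstract, objectives and efficacy definition describe an efficacy trial judged by significance. As written, the headline results would be contrasts with a 95% CI of about ±0.78 SD, in a trial whose stated detectable effect is about 1.1 SD. Recruitment and retention have no declared outcome, and acceptability has no measure at all.

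The text comparison needs no assumption. The figures assume a two-sided 5% level, 80% power, an unadjusted two-sample t test and complete data on 14 per arm. Missing data would widen the interval; adjustment for baseline could narrow it. The change should be made, and it is worth making before the data are analysed.

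**What to change.** 1. **Reconcile the text.** Bring the abstract, Objectives and Efficacy Assessments/Measurement of Effect into line with the sample size section. Report EEG, PANSS, NSA-16 and CFS as effect estimates and SDs with 95% CIs for planning, and draw no efficacy conclusion from significance tests.
2. **Add declared feasibility outcomes beside the registered ones**, each with a 95% CI:
   - consent among those approached or potentially eligible, with the denominator stated;
   - retention at week 17 among those randomised;
   - number of the 16 sessions completed with the full 20-minute stimulation from the device log (for sham, the full sham programme), labelled as the acceptability proxy, since it shows adherence rather than opinion;
   - adverse events.
3. **Date the change** as an amendment made after enrolment began.

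I would not turn the planning figures into pass marks. If true consent were 22% of 150, a rule of at least 22% (33 or more) would fail about 47% of the time. If true retention were 80% of 28, a rule of at least 80% (23 or more) would fail about 50% of the time.

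The cost is an amendment, a registry update and a more modest efficacy claim. No new data are needed: screening and enrolment logs, withdrawal forms, device logs and safety records are already provided for.
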